## Abstract

**Background:**

The first aim of this study is to test the effectiveness of school-based psychosocial interventions for improving mental health in rural Chinese children with traumatic experiences. The second aim is to examine which individual, family and school related factors could explain the effectiveness of school-based psychosocial interventions. Third, we will investigate whether individual, family, and school related conditions play a moderator role on the effectiveness of school-based psychosocial interventions.

**Methods:**

This study will conduct a cluster randomized controlled trial (RCT) in a large sample of Chinese rural children. Four rural counties in Shandong (Central China), Henan (Central China), Inner Mongolia (Northern China), and Xinjiang (Western China) will be selected as study settings from which schools will be sampled. Each sampled school will be randomly allocated either the intervention groups or a control group. Randomization will be performed by the research member who is not involved in the intervention stage. In each school students in grade 5 or higher will be recruited to ensure that approximately 50 children aged 10 to 18 years will be included. In each county, one high school, one middle school, and one primary school will be randomly chosen as the intervention group, and the other three similar schools will be chosen as control (waiting list) groups. A standardized and uniform research protocol will be applied in all intervention schools. All school social workers and psychological teachers would receive one week of in-person training following procedures. School-based psychosocial interventions included 14 group sessions for 14 consecutive weeks.

**Discussion:**

This study would develop school-based mental health promotion policy recommendations to improve Chinese rural children’s mental health. This study can provide solid evidence for the promotion of school-based intervention in general.

**Trial registration:**

ChiCTR2300069405, Registered on 15 March 2023.

## Background

Trauma survivors are at high risk of many adverse mental health outcomes, most prominently posttraumatic stress symptoms(PTSS), self-injurious behavior, and other psychotic symptoms [1, 2]. Experiencing trauma in childhood—a crucial period for the developing brain and personality—is a key risk factor for developing psychopathology later in life [1]. Chinese families and governments have suffered enormous economic and social losses from the negative consequences of childhood trauma. One study estimated that emotional and physical abuse in childhood accounts for 26.3% and 12.2% of the disability-adjusted life-years (DALYs) lost because of mental disorders [3]. China lost 0.84% of Gross Domestic Product (GDP) due to child physical abuse and 0.47% and 0.39% of GDP due to child emotional abuse and child sexual abuse, respectively [3]. These findings indicate that it is necessary to establish beneficial interventions to reduce the likelihood of developing psychopathology among victimized children. Meta-analyses of worldwide samples show self-reported rates of 22.6% for physical abuse, 16.3% for physical neglect, and 18.4% for emotional neglect [4]. In China, a recent meta-analysis revealed that the pooled prevalence of child physical abuse, physical neglect, and emotional neglect were 20%, 47%, and 44%, respectively [2]. Thus, it is necessary to identify and conduct intervention programs for improving mental health status among Chinese victimized children.

### Effectiveness of school-based psychosocial interventions on mental health among children

Schools are a safe environment and can provide supportive trainings and interventions to universal children. School-based psychosocial interventions for traumatic psychological usually involve three types of interventions: preventive interventions in school or classroom level, universal psychosocial support interventions, and targeted trauma-focused cognitive behavioral therapy (TF-CBT) [5]. In particular, trauma-focused CBT has been proven to be an effective treatment of many commonly experienced mental problems by traumatized children, such as PTSD, depression [6]. Although TF-CBT approach is increasingly recommended, few studies have evaluated the effectiveness of multilayered interventions. In addition, the effectiveness of these interventions relies on not only the intervention content but also implementers. The worldwide shortage of mental health professionals limits the development of primary mental health services. In China, child mental health human resources are scarce, with fewer than 500 full-time child psychiatrists in the whole country [7]. Especially unique to Chinese children are the salient mental health disparities between urban and rural areas, and rural children experience more childhood trauma [2, 8]. Moreover, child psychiatrists are unequally distributed in China, as most of them are concentrated in major cities such as Beijing, while in rural areas, there are no specialist child psychiatry services [7]. Therefore, cluster randomized clinical trials in school settings by school social workers and headteachers may be a cost-effective and feasible way to improve rural children’s mental health.

The results of previous school-based intervention studies seem inconsistent and lack statistical power. One study suggests that a multilayered psychosocial care package seems feasible and satisfactory in reaching out to substantial populations of distressed children through different levels of care [9]. Another study found that the school-based psychosocial intervention provided by paraprofessionals helps maintain hope and reduce PTSD symptoms in children affected by political violence [10]. However, other results suggest that the comprehensive school-based intervention model was effective, although different service components affected different student outcomes. One study conducted among refugee youths reported that students across all tiers of the program demonstrated improvements in mental health and resources. However, the sample size per tier was small, and comparative analyses between tiers were not possible to conduct [11]. In addition, few studies that have tested the effectiveness of school-based psychosocial interventions among Chinese children [12] are based on small sample sizes and short-term follow-ups, limiting the validity and generalizability of the results. In this study, we will perform a classroom-based, preventive intervention that provides tools to create a safe classroom environment for children.

### Mechanism of psychosocial interventions at multiple levels

Strong evidence was found for several mechanisms explaining the effectiveness of psychosocial interventions to improve mental health among traumatized children. The first mechanism improves children’s capacities, including resilience, improving unfavorable personality traits, effective coping style, and mastery of traumatic experiences. Resilience is a crucial aspect in the child psychopathology area [13]. Some studies have shown that higher levels of resilience are related to fewer depressive and/or anxiety symptoms [14, 15]. Extensive evidence from a longitudinal study confirmed that resilience reduced the risk of depressive symptoms in individuals with childhood trauma experience [16]. In addition, personality traits reflecting stress control and self-regulation abilities are also important [17]. A study found that children with adaptive personality traits were liable to experience positive emotions, obtain social interaction and adopt an effective problem-solving method when encountering adversities [15]. Moreover, growing evidence has begun to show that factors related to children’s capacities, such as coping ability, might offer new psychosocial interventions to prevent and improve children’s mental health [18].

The second mechanism of effective psychosocial interventions in children is enhancing family capacity, which involves support for parents’ and caregivers’ ability through psychoeducation and communication skills. Parents are usually the ones who interact the most with children and adolescents. Offering group interventions to parents may be an effective way to support them and their children by sharing experiences in a similar situation [19] and learning how to support their child in managing psychological symptoms [20–22]. The World Health Organization (WHO) advises parents to communicate with their children in an honest and age-appropriate way that addresses children’s concerns and eases their anxiety. In this way, close and open communication between parents and children may serve as a protective factor in children’s mental health [23]. Research suggests that parent‒child discussions could change individuals’ perceptions and cultivate positive mindsets, which in turn reduce children’s depressive, anxiety, and stress symptoms [24]. Therefore, interventions to enhance family capacity, such as parent‒child communication skills, could help traumatized children cope with mental health problems.

The third mechanism is strengthening family relationships, which is especially important in facing traumatic events. A growing body of evidence highlights the important role of families in the prevention of internalizing problems, of which family relationships were the most frequently reported to be associated with mental health symptoms among children and adolescents [25, 26]. Zheng Ren’s study selected middle school students as participants and found that poor parent‒child relationships were associated with an increased risk of depressive symptoms [27]. Additionally, poor parental relationships may expose children to negative feelings about traumatic events and worse their mental health symptoms [27]. Thus, given the direct and indirect effect of family relationships on mental health problems among children, urgent consideration should be given to facilitate better family relationships, especially when facing traumatic events.

The fourth mechanism is providing a supportive environment, which is indicated by trusting relationships with therapists, teachers, and others. In schools, teaching social, emotional and behavioral control skills contributes to the development of personal relationships among students, as they provide the opportunity for students to discuss difficult feelings in a safe and supportive environment [28]. Adolescents face important interpersonal challenges, including the renegotiation of relationships with parents and increased involvement with peers and friends [29]. According to research findings, a supportive relationship between children and teachers is associated with a reduction in aggressive behavior [30] and can contribute to preventing behavior problems and enhancing students’ psychosocial development and adaptation [28]. Negative relationships with teachers constitute a predictive factor of the onset of psychiatric disorders and school failure [31]. In addition, teachers more actively promote mental health in the presence of positive personal relationships [32]. Therefore, more attention should be given to recruiting and preparing teachers or therapists capable of establishing trusting and supportive relationships with traumatized children.

Thus, conducting school-based psychosocial interventions from the above four perspectives are feasible and effectiveness methods. First, we will provide mental health knowledge and communication skills for children to encourage them talk their difficulties to parents, school counselor, or health care provider. Second, we plan to introduce the child mental health symptoms to parents, so that they can understand their children’s problem. Third, emotional expression and communication skills training will be employed to enhance family relationship. Forth, series training will be set up to build a supportive environment, which will help teachers to identify mental health risk and conduct regular psychological counseling for students.

## Aims and hypotheses

Based on the evidence and research gaps presented above, the aim of the current study is to explore the effectiveness of school-based psychosocial interventions on PTSS and other mental health statuses in Chinese rural children who experienced a traumatic event. To achieve this aim, we will conduct a cluster RCT in a large sample of Chinese rural children. The criteria for intervention effectiveness were reducing mental health problems through increasing positive coping style or resilience compared to children in waiting-list schools. The second aim is to examine which school-related and individual factors could explain and affect the effectiveness of school-based psychosocial interventions. Third, we analyze whether individual, family, and school-related conditions moderator the effectiveness of school-based psychosocial interventions. Specifically, we answer the following study questions and test the corresponding hypothesis:

Do school-based psychosocial interventions have a positive effect on children’s mental health? (a) We hypothesize that posttraumatic stress symptoms will decrease significantly among children in intervention schools but not in control schools. (b) We hypothesize that other mental health problems, such as depressive symptoms, anxiety symptoms, and bullying behaviors, will decrease significantly among children in intervention schools but not in control schools.Do multilayered related factors have a mediating effect on children’s mental health? We hypothesize that the participation of students, parents, school social workers and headteachers in the psychosocial interventions increases their sense of self-efficacy, communication skills, and decreases their stress, which in turn are associated with decreased mental health symptoms among the children in the intervention schools.Do multilayered related factors moderate the psychosocial intervention effect on children’s mental health? We hypothesize that the individual, family and school social workers’ and headteachers’ characteristics and the school’s environment are associated with stronger changes in the relationship between positive coping, resilience and mental health symptoms among the children in the intervention schools.

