### Sample sizes and subjects

The required sample size to detect an expected intervention effect with sufficient statistical power was calculated for the primary outcome posttraumatic stress symptoms, as measured with the PTSD Checklist for DSM-5 (PCL-5) scale, using a method that considers the estimation of effect size, repeated measurements, significance level, power, allocation ratio, and attrition rate at T2, and T3. The following parameters are used: (1) the effect size estimations for the primary outcome is 0.20 (based on a meta-analysis [33]); (2) the intraclass correlation is 0.05; 4) 5% level of significance; 5) 80% level of power; 6) allocation ratio of 1:1; and 7) attrition rate of 20%. Under these hypotheses, we expect a sample size of at least 24 clusters (i.e., schools) with 50 children in each school to be included, resulting in a total intended sample size of 1200 children, 1200 parents and 30 teachers. The sample size will be distributed as evenly as possible among the control schools and intervention schools.

Eligibility criteria: As school is our intervention unit, the inclusion criterion is that the school should not have a similar psychosocial intervention program. For students, all children in the program schools who have signed informed consent will participate in this program. Exclusion criteria: Children with severe physical and mental health problem, and unable to participate into the program completely.

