### Assessments

In this study, we will assess parents, children, and teachers. The assessments were taken before (T1 = one week before intervention), after (T2 = one week after intervention), and follow-up the interventions (T3: six weeks after intervention). To reduce recall bias for health data, we will also combine children’s electronic medical records. The research tools are shown in Table 2. We will use measurement instruments that are well-validated and reliable instruments. The control variables mainly include children’s, parental and teacher’s socio-demographic characteristics. Moderator and mediator variables include children’s resilience, coping methods, family environment, school environment, etc.

**Table 2 Tab2:** Assessment tools

Category	Variables	Indicator/tools	Data sources
**Outcomes**	PTSS	PTSD Checklist for DSM-5 (PCL-5)	Parents/Child
	Depression	10 Items The Center for Epidemiological Studies-Depression (CESD-10), The Strengths and Difficulties Questionnaire (SDQ)	Child
	Anxiety	Self-Rating Anxiety Scale (SAS)	Child
	Bullying	Delaware bullying victimization scale	Child
**Predictors**	Trauma event	PCL-5 checklist	Child
	Intervention related	Participate, Stratification	Child/teacher
**Confounding**	Child characteristics	Gender, age et al.	Child
	Parent characteristics	Gender, age, marital status et al.	Parent
	Teacher characteristics	Gender, age, teaching background et al.	Teacher
**Moderator/Mediator**	Resilience	14-Item Resilience Scale (RS-14)	Child
	Coping style	Simplified Coping Styles	Child
	Family environment	Family Functioning Style Scale	Child
	School environment	Delaware School Climate scale	Child

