### Statistical methods

All analyses are on an intention-to-treat basis, with all randomized participants included in the analysis and analyzed according to original group assignment regardless of treatment dose received. Descriptive statistics will be used to summarize the characteristics of the participants. Generalized linear mixed models (GLMMs) will be used to evaluate the effectiveness of the intervention on outcomes using a three-level multilevel model. This model includes intervention status, time, and the treatment between intervention and time as fixed effects. Dependency in the repeated measurements within individuals will be modeled using a random intercept and random slope at the participant level. A random intercept at the school level will be used to model dependencies between children within the same school. The interaction between treatment and schools will also be tested to investigate the cluster effects. Confounders will also be included as fixed effects in the model, including gender, age, parent characteristics, and teacher characteristics. The estimated intervention effect will be reported as the mean outcome differences (at T2, T3) and 95% confidence interval (95% CI) between the intervention and control groups. All covariate-by-condition interactions on child mental health will be examined.

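### The stated hypotheses and effectiveness criterion set a success rule that differs from the planned between-arm analysis, and the protocol does not say which governs

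*Protocol article*

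**What the plan says.** In the protocol article, Aims and hypotheses announces that hypotheses will be tested. Hypothesis (a) is that "posttraumatic stress symptoms will decrease significantly among children in intervention schools but not in control schools". Hypothesis (b) says of depression, anxiety and bullying that they "will decrease significantly among children in intervention schools but not in control schools".

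The same section gives a criterion of success: "The criteria for intervention effectiveness were reducing mental health problems through increasing positive coping style or resilience compared to children in waiting-list schools". The Assessments section gives those two variables another role: "Moderator and mediator variables include children’s resilience, coping methods, family environment, school environment, etc".

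The Statistical methods describe a three-level mixed model: "This model includes intervention status, time, and the treatment between intervention and time as fixed effects" (the third term is evidently the interaction of arm with time). The effect is to be "reported as the mean outcome differences (at T2, T3) and 95% confidence interval (95% CI) between the intervention and control groups". Under Sample sizes and subjects, "the effect size estimations for the primary outcome is 0.20", with the PCL-5 named as the primary outcome.

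**The concern.** A significant fall in one arm and a non-significant fall in the other is not evidence that the arms differ. Two arms with the same true fall can land on opposite sides of p = 0.05 by chance. Two arms that do differ can both show significant falls, and the hypothesis as worded then fails. Symptoms may fall in both arms over a semester, for instance through maturation or repeated testing. A randomised control group exists to remove such a trend, and a within-arm rule lets it back in.

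The effectiveness criterion raises a second difficulty. Read literally, it credits a reduction in symptoms only when it comes through coping or resilience. The Background names further mechanisms: family capacity, family relationships and a supportive environment. Benefit by those routes would not meet the criterion, although the between-arm difference in PCL-5 would capture it.

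At stake is the primary claim. The article offers a within-arm rule, a mediated criterion and a between-arm estimate, and these can disagree on the same data.

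**Working it through.** **Passages compared.** Hypotheses (a) and (b) need two separate results, a significant fall in one arm and none in the other. The effectiveness criterion is comparative but requires a route through coping or resilience. The Statistical methods estimate one quantity, the difference between arms, at T2 and T3. The sample size uses one standardised effect and no mediated effect. No sentence ranks these.

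**The plan's own figure.** The article gives no error rate for its within-arm rule, so there is none to reproduce. The figures below show what the rule would do if it were applied.

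**Inputs from the article:** 24 schools, 1:1, so 12 per arm; 50 children per school with 20% attrition, so 50 × 0.8 = 40; ICC 0.05; effect 0.20 SD; 5% level (sidedness not stated; two-sided assumed).

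**Assumptions not in the article:** correlation over time of 0.6 for the child component and 0.5 to 0.8 for the school component; an equal fall in both arms of 0 to 0.30 SD.

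**Standard error of a within-arm change, in SD units:**

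SE = √{[2 × ICC × (1 − r_school) + 2 × (1 − ICC) × (1 − r_child)/40] / 12}

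- r_school = 0.8: √[(0.020 + 0.019)/12] = 0.057
- r_school = 0.5: √[(0.050 + 0.019)/12] = 0.076

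**Probability that an arm with true fall δ shows a significant decrease:** p(δ) = P(T > 2.201), where T is noncentral t on 11 df with noncentrality δ/SE.

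**The literal rule,** for common fall c:

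- no true difference: P(false success) = p(c) × [1 − p(c)]
- true effect 0.20: P(rule met) = p(c + 0.20) × [1 − p(c)]

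Each cell gives r_school = 0.5, then 0.8.

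| Common fall c (SD) | p(c) | False success, % | Rule met with true 0.20 SD effect, % |
|---|---|---|---|
| 0 | 0.0250; 0.0250 | 2.4; 2.4 | 65.4; 86.8 |
| 0.05 | 0.0875; 0.1236 | 8.0; 10.8 | 77.6; 85.7 |
| 0.10 | 0.2253; 0.3601 | 17.5; 23.0 | 73.5; 63.8 |
| 0.15 | 0.4386; 0.6691 | 24.6; 22.1 | 55.4; 33.1 |
| 0.20 | 0.6712; 0.8905 | 22.1; 9.8 | 32.8; 11.0 |
| 0.25 | 0.8506; 0.9782 | 12.7; 2.1 | 14.9; 2.2 |
| 0.30 | 0.9487; 0.9975 | 4.9; 0.3 | 5.1; 0.3 |

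The ceiling on false success is p(1 − p) = 0.5 × 0.5 = 25%, whatever the correlations.

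**Comparison.** A two-sided 5% between-arm test errs in favour of the intervention 2.5% of the time at every common fall, because the fall cancels. Its power does not move with the trend either. On change scores with the same inputs, SE = √2 × 0.076 = 0.107 or √2 × 0.057 = 0.081, giving power of 43% or 66% on 22 df for an effect of 0.20. These serve only to show stability. They do not reproduce the sample size, whose repeated-measures correlation is not given.

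**Check with a simpler variance.** With one pre-post correlation r, SE = √[2(1 − r) × DE/n], where DE = 1 + 39 × 0.05 = 2.95 and n = 12 × 40 = 480. At r = 0.6 this is √[0.8 × 2.95/480] = 0.070. Using normal probabilities, false success is 20.9% at c = 0.10, and the rule is met 18.6% of the time at c = 0.20 with a true 0.20 effect. The pattern is the same.

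**The mediated criterion.** Its power cannot be computed, because the article gives no effect of the intervention on coping or resilience and none of these on symptoms.

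**The case against.** The strongest reply is that the analysis is already between-arm. The Statistical methods plan no within-arm test, and "The estimated intervention effect will be reported as the mean outcome differences (at T2, T3) and 95% confidence interval" describes a proper contrast. The effectiveness sentence itself ends with a comparison against waiting-list schools. The hypotheses can be read as expectations, and mediation has its own study question. All of this stands. A reader might infer that the trial will be judged on two within-arm p-values and so can claim success with no difference between arms. The documents do not support that, because nothing tells the analyst to set aside the mixed-model contrast.

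The reply does not remove the conflict. The hypotheses are introduced as what will be tested, the within-arm form appears twice, and the only sentence on criteria for effectiveness is the one tied to coping or resilience. The Statistical methods give a model and a reporting format but do not say that they override this. An analysis plan may add detail; here the published text itself states an invalid comparison.

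The error rates also depend on the assumed common fall. With none, the literal rule gives false success of about 2.4%, and with a true effect it is met more often than the between-arm test would be. A narrow choice of common falls would make the case look one-sided, so the full range is shown.

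A reader might also count two informants by two time points as four primary tests. That is not supported. The article names one primary outcome. The Parents/Child entry for the PCL-5 in Table 2 may mean parents' reports on the child or parents' own symptoms. Naming a deciding time point or informant may properly be left to the analysis plan.

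**Conclusion.** The point holds as an unreconciled conflict within the protocol article. Hypotheses (a) and (b) compare within-arm significance, and the effectiveness criterion builds in mediation; the Statistical methods and the sample size rest on a between-arm effect. No passage says which governs.

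The consequences are conditional on the hypotheses being applied literally. False success would then be about 2% with no common fall, nearly 25% at its peak, and 0.3–5% at a common fall of 0.30 SD. A true 0.20 SD effect would meet the rule 65–87% of the time with no common fall and 11–33% at 0.20 SD. These figures rest on the assumed correlations and common fall; only the 25% ceiling is free of assumed correlations. If the mixed-model contrast decides, none of this harm arises and the defect is one of wording, though in the statement of the primary claim.

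**What to change.** Restate hypothesis (a) as a between-arm difference in mean PCL-5, intervention minus control, below zero, estimated by the mixed model in the Statistical methods and tested at the stated 5% level. Word (b) in the same way for the other outcomes. Say that within-arm changes are descriptive. Take the coping and resilience clause out of the effectiveness criterion and place it under the mediation question. Add one sentence saying that the between-arm contrast decides effectiveness. Which time point and informant are decisive is the sponsor's choice.

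The cost is protocol wording only. It needs no new data, no change to the model and no change to the sample size. The sponsor gives up one route to a positive claim, and that route is not a valid one.

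### The mediation and moderation hypotheses cannot be tested as worded: the named mediators have no listed instrument, and both hypotheses are confined to intervention schools

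*Protocol article*

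**What the plan says.** Under Aims and hypotheses, the article poses three study questions, each with a hypothesis. Hypotheses 2 and 3 below are the second and third of these.

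- **Hypothesis 2 (mediation).** Involvement of students and parents, and of "school social workers and headteachers in the psychosocial interventions increases their sense of self-efficacy, communication skills, and decreases their stress". These changes are then tied to the outcome by the clause "which in turn are associated with decreased mental health symptoms among the children in the intervention schools".
- **Hypothesis 3 (moderation).** Characteristics of the child, the family, the social workers and headteachers, and the school environment "are associated with stronger changes in the relationship between positive coping, resilience and mental health symptoms among the children in the intervention schools".

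The aims in the same section are broader: "The second aim is to examine which school-related and individual factors could explain and affect the effectiveness of school-based psychosocial interventions", and "Third, we analyze whether individual, family, and school-related conditions moderator the effectiveness of school-based psychosocial interventions". That section also judges effectiveness by fewer mental health problems, reached through better coping or resilience, relative to the waiting-list schools.

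Under Assessments, the groups assessed are parents, children and teachers, and "Moderator and mediator variables include children’s resilience, coping methods, family environment, school environment, etc". Table 2 names one scale for each of these four constructs and gives the child as the data source for all of them.

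Under Statistical methods, the mixed model contains arm, time and their interaction, and "All covariate-by-condition interactions on child mental health will be examined".

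**The concern.** There are two separate faults. First, the mediators that are hypothesised are not the mediators that are listed for measurement. An analysis plan written later cannot recover a construct that was never collected, so this cannot be left to that plan. Second, mediation or moderation of an intervention effect is defined by comparing arms. A hypothesis restricted to the treated schools has no such comparison and can show only correlations among treated children.

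At stake is what the trial may conclude on its secondary questions. If the wording stands, a report could present a within-arm association as a mechanism of the intervention, or could test substitute constructs under a hypothesis that names different ones. The primary comparison on posttraumatic stress symptoms does not depend on either hypothesis.

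**Working it through.** No figure in the plan needs reproducing. The check sets the hypotheses beside the measures and the model.

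**Step 1. Constructs and groups against Table 2.** Hypothesis 2 names 3 constructs (self-efficacy, communication skills, stress) in 4 groups, so 3 × 4 = 12 pairings need a measure.

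| Group in hypothesis 2 | What Table 2 lists from that group | Instrument for any of the 3 constructs |
|---|---|---|
| Students | Symptom and bullying outcomes, trauma events, intervention-related data, background, the four moderator/mediator scales | None listed |
| Parents | PCL-5 (shared with the child), background | None listed |
| Headteachers (as teachers) | Background, intervention-related data | None listed |
| Social workers | Nothing; not an assessed group | None listed |

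Result: 0 of 12. The PCL-5 and the anxiety scale come closest to stress, but both are listed as outcomes, and an outcome cannot also serve as its own mediator.

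**Step 2. The reverse match.** Table 2 lists 4 moderator/mediator constructs. All 4 are child-reported, and none is a mediator named in hypothesis 2. Two of them, coping and resilience, do appear in the effectiveness criterion, so the article holds two different accounts of the mechanism.

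**Step 3. What the restriction to one arm removes.** Let A be arm (1 = intervention), M1 and M2 the T1 and T2 values of a scale, and Y the symptom score.

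- *Moderation:* Y = b0 + b1·A + b2·M1 + b3·A·M1. The moderation effect is b3. If every school has A = 1, this becomes Y = (b0 + b1) + (b2 + b3)·M1, and b3 cannot be separated from b2.
- *Mediation:* M2 = a0 + a·A and Y = c0 + c·A + b·M2. In this linear form the indirect effect is a × b. With A = 1 throughout, a is absorbed into the intercept, leaving only b, an association among treated children.

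**Step 4. Consistency between sections.** Three statements of the moderation target differ:

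- the study question and aim 3 concern what modifies the intervention's effect, which needs both arms;
- hypothesis 3 concerns what modifies the link from coping and resilience to symptoms, within treated schools;
- Statistical methods plans covariate-by-condition interactions, which need both arms.

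Only the hypothesis is confined to one arm. For mediation the split is the same: the effectiveness criterion compares arms and hypothesis 2 does not. So 2 of 2 hypotheses are out of line with the rest of the article.

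**The case against.** The strongest reply is that a condensed article should not be read this literally. The list of moderators and mediators is open-ended. The section on pilot and screening says that the mental health status of parents and teachers will be surveyed. The family functioning scale might touch on communication; the article does not show its content. The closing phrase of each hypothesis may be loose drafting, since the aims, the effectiveness criterion and the model all compare arms.

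Part of this stands. It rules out saying that the constructs are not measured at all; the supportable statement is that no instrument is listed. It does not remove the mismatch. Table 2 names a tool for every outcome and every moderator/mediator, the open-ended list follows child and environment variables, and the adult survey is described as baseline data with no tool, whereas a mediator has to be measured after treatment starts. If the closing phrases are loose drafting, correcting them costs nothing.

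Three stronger readings are tempting and should be resisted.

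- *Aims 2 and 3 cannot be answered.* The aims are tied neither to the three constructs nor to one arm, nothing limits the four scales to intervention schools, and the planned interactions are a two-arm moderation analysis.
- *Post-treatment values will be used as moderators.* Table 2 uses one joint label for moderators and mediators, but nowhere says that T2 values will act as moderators. Which visit serves which role may be left to the analysis plan.
- *A given number of false-positive interactions.* The covariate rows in Table 2 are open-ended, separate tests at T2 and T3 are not stated, and the tests would be correlated. No count or error rate follows from the article.

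**Conclusion.** Hypotheses 2 and 3 are wrong as written. Hypothesis 2 has a listed instrument for 0 of its 12 construct-by-group pairings, and one of its four groups is not assessed. Both hypotheses omit the between-arm contrast that the study questions need and that other parts of the article use. The damage is confined to the secondary aims, which remain partly answerable through resilience, coping, family functioning and school climate in both arms.

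This rests on Table 2 being the list of instruments that the trial will use. If the full protocol names tools for self-efficacy, communication skills and stress, including for social workers, after treatment starts and in both arms, the measurement half falls away. The arm-restriction half would remain.

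**What to change.** 1. **Hypothesis 2.** Restate it around the four listed constructs as a two-arm mediation question: arm to T2 mediator to T3 PCL-5, adjusting for the T1 mediator and T1 PCL-5. State that only the arm-to-mediator step is protected by randomisation; the mediator-to-outcome step assumes no unmeasured common causes.
2. **Hypothesis 3.** Restate it as arm-by-moderator interactions on child symptoms in both arms, using T1 values of the moderators, consistent with Statistical methods and reported as exploratory.

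The four scales and the three visits are already in the plan, so the cost is wording and no new data. The real price is scope: the mediation claim narrows to what children report and no longer speaks to change in parents, social workers or headteachers.

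The alternative is to keep hypothesis 2's constructs and add instruments for all four groups, in both arms and after treatment starts. That adds burden, and the staff-level part would carry little information: Sample sizes and subjects plans 30 teachers across 24 schools, or 30 / 24 = 1.25 per school.
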